### Analysis of Secondary Outcomes

#### Analysis for Binary Categorical Outcomes

A similar analytic strategy as for the primary outcome will be followed for other binary outcomes. These include the proportion of FBG<7.0 mmol/L, BP<140/80 mmHg, and that of LDL-C<2.6 mmol/L, and the optimal control rate of combined ABC targets. A log-binomial regression with GEE and including baseline continuous values of the analyzed outcome variable as covariate (model 1) will be used. Other further adjusted analysis (model 2) and subgroup analysis will also be conducted, and the imputed analysis as well, if applicable.

#### Analysis for Continuous Outcomes

HbA_1c_, FBG, BP, and LDL-C will also be analyzed as continuous variables. A similar analytic strategy as the one used for binary outcomes will be followed but using a linear regression (ie, assuming a normal distribution and an identity link, instead of a log-binomial regression). The raw mean (SD) of the changes will be reported. The effect of the intervention will be presented as the adjusted mean difference and associated 95% CIs. Further covariates-adjusted analyses (see model 2) and subgroup analysis will also be conducted, and the imputed analysis as well, if applicable.

#### Analysis of Hypoglycemia

Episodes of hypoglycemia (each subtype and overall) will be analyzed with the same approach as before; this time using Poisson regression adjusted for the baseline count of hypoglycemia. The effect of the intervention will be estimated as the incidence rate of hypoglycemia episodes and its 95% CI. The number of patients experiencing at least one hypoglycemia episode and the total number of episodes will be tabulated by group. Adjusted analysis and subgroup analysis will also be conducted. No imputation will be performed on hypoglycemia.

### Analysis of Other Outcomes

No subgroup and imputed analysis will be performed on the following endpoints.

#### EQ-5D

The EQ-5D index value and EuroQol-visual analogue scale (EQ-VAS) score at baseline and at end-of-study will be described using mean and SD by treatment groups. For changes in EQ-5D index values and VAS scores, a linear regression with GEE accounting for clustering will be used to test the difference between groups. The baseline values of the outcome variable will be included as covariates. The raw mean (SD) of the score changes will be reported by treatment groups; the effect of the intervention will be presented as the mean differences of the changes and associated 95% CIs.

#### The Summary of Diabetes Self-Care Activities

The scores of the summary of diabetes self-care activities questionnaire will be described at baseline and 1 year. For their changes from baseline, a linear regression with GEE and with adjustment of the baseline values of analyzed outcome variables will be used to compare the difference between treatment groups. Other covariates with further adjusted models will also be conducted. The raw mean (SD) of the score changes will be reported by treatment groups; the effect of the intervention will be presented as the mean differences and associated 95% CIs from the two previously mentioned models.

#### Other Variables

The following outcomes will be analyzed using descriptive statistics without any adjustment for clustering.

Concomitant medications. Insulin injection and oral antidiabetic drug intake at baseline and at end-of-study assessments. The combination of different oral antidiabetic drug regimens or the combination of insulin injection and oral antidiabetic drugs, or their single use will also be summarized.New-onset comorbidities and diabetic complications will be described as the numbers and percentages of patients with each new onset complication by treatment groups.Direct medical cost is the self-reported direct cost on medication and medical expense for health care services (inpatient or outpatient cost, medication cost), including total cost and out-of-pocket cost.

## Results

This study was funded in January 2017. Ethics approval was obtained from the Institutional Review Board at Shanghai Sixth People's Hospital, where the lead PI is affiliated with, before the study commenced. Written approval from each participating site was granted by the local hospital research ethics committee, and other relevant regional regulatory bodies. Signed informed consent was obtained from all trial participating doctors and patients prior to participant recruitment. Recruitment commenced in June 2017 and closed after completed baseline assessment in December 2018 for all 864 trial participating communities in 144 districts or counties in 25 provincial sites (1 more province than the scheduled 24 because of a shortage in eligible district or county hospitals). As of October 2019, the last 1-year end-of-study assessment ended. The internal statistical plan was reviewed, approved, and signed off in November 2019 and made public on the institutional internal website prior to the database lock in January 2020.

Templates of main tables (ie, baseline characteristics as in Table 1, estimated intervention effects for binary outcomes as in Table 2, estimated intervention effects for continuous outcomes as in Table 3, and hypoglycemia incidence as in Table 4) were produced prior to the previously mentioned analytical methods.

**Table 1 table1:** Baseline characteristics of participants by treatment arms in the road to hierarchical diabetes management at primary care study.

Characteristics				Control (xxxx)		Intervention (xxxx)		Standardized differences
**Region by economic development, n (%)**							x.xxx	
	Developed		xxx (xx.x)		xxx (xx.x)			
	Less developed		xxx (xx.x)		xxx (xx.x)			
**Locality, n (%)**							x.xxx	
	Urban		xxx (xx.x)		xxx (xx.x)			
	Rural		xxx (xx.x)		xxx (xx.x)			
**Demographics**								
	Age (years), mean (SD)		xx (xx)		xx (xx)		x.xxx	
	Gender (male), n (%)		xxx (xx.x)		xxx (xx.x)		x.xxx	
	BMI (kg/m^2^), mean (SD)		xxx (xxx)		xxx (xxx)		x.xxx	
	**Highest level of education, n (%)**						x.xxx	
		Primary school or lower	xxx (xx.x)		xxx (xx.x)			
		Junior high school	xxx (xx.x)		xxx (xx.x)			
		Senior high school	xxx (xx.x)		xxx (xx.x)			
		Junior college and above	xxx (xx.x)		xxx (xx.x)			
	Annual income per capita (CNY), mean (SD)		xxx (xxx)		xxx (xxx)		x.xxx	
	Health insurance coverage (Yes), n (%)		xxx (xx.x)		xxx (xx.x)		x.xxx	
	**Insurance reimbursement rates, n (%)**						x.xxx	
		70%-100%	xxx (xx.x)		xxx (xx.x)			
		50%-70%	xxx (xx.x)		xxx (xx.x)			
		<50%	xxx (xx.x)		xxx (xx.x)			
**Self-reported medical history and complications**								
	Duration of diabetes (years), median (Q1, Q3)		xxx (xxx, xxx)		xxx (xxx, xxx)		x.xxx	
	Current smoker, n (%)		xxx (xx.x)		xxx (xx.x)		x.xxx	
	Hypertension, n (%)		xxx (xx.x)		xxx (xx.x)		x.xxx	
	Dyslipidemia, n (%)		xxx (xx.x)		xxx (xx.x)		x.xxx	
	Diabetic nephropathy, n (%)		xxx (xx.x)		xxx (xx.x)		x.xxx	
	Diabetic retinopathy, n (%)		xxx (xx.x)		xxx (xx.x)		x.xxx	
	Peripheral neuropathy, n (%)		xxx (xx.x)		xxx (xx.x)		x.xxx	
	Lower extremity, n (%)		xxx (xx.x)		xxx (xx.x)		x.xxx	
	Macro-vascular, n (%)		xxx (xx.x)		xxx (xx.x)		x.xxx	
**Lab characteristics**								
	HbA_1c_^a^ (%), mean (SD)		x.xx (x.xx)		x.xx (x.xx)		x.xxx	
	HbA_1c_<7%, n (%)		xxx (xx.x)		xxx (xx.x)		x.xxx	
	FBG^b^ (mmol/L), mean (SD)		x.xx (x.xx)		x.xx (x.xx)		x.xxx	
	FBG<7.0 mmol/L, n (%)		xxx (xx.x)		xxx (xx.x)		x.xxx	
	SBP^c^ (mmHg), mean (SD)		xxx (x.xx)		xxx (x.xx)		x.xxx	
	DBP^d^ (mmHg), mean (SD)		xxx (x.xx)		xxx (x.xx)		x.xxx	
	LDL-C^e^ (mmol/L), mean (SD)		x.xx (xxx)		x.xx (xxx)		x.xxx	
	LDL-C<2.6 mmol/L, n (%)		xxx (xx.x)		xxx (xx.x)		x.xxx	
	Serum creatinine (umol/L), median (Q1, Q3)		xxx (xxx, xxx)		xxx (xxx, xxx)		x.xxx	

^a^HbA_1c_: glycated hemoglobin.

^b^FBG: fasting blood glucose.

^c^SBP: systolic blood pressure.

^d^DBP: diastolic blood pressure.

^e^LDL-C: low-density lipoprotein cholesterol.

**Table 2 table2:** Estimated effects of intervention compared to control on primary and secondary binary outcomes at end of study.

Outcomes			Control, n (%)	Intervention, n (%)	Primary model^a^	
					RR^b^ (95% CI)	*P* value
**Primary outcome**						
	HbA_1c_^c^ < 7.0%		xxx (xx.x)	xxx (xx.x)	x.xx (x.xx-x.xx)	.xx
**Secondary outcomes**						
	FBG^d^ < 7.0 mmol/L		xxx (xx.x)	xxx (xx.x)	x.xx (x.xx-x.xx)	.xx
	BP^e^ < 140/80 mmHg^f^		xxx (xx.x)	xxx (xx.x)	x.xx (x.xx-x.xx)	.xx
	LDL-C^g^ < 2.6 mmol/L		xxx (xx.x)	xxx (xx.x)	x.xx (x.xx-x.xx)	.xx
	Composite diabetes control^h,i^		xxx (xx.x)	xxx (xx.x)	x.xx (x.xx-x.xx)	.xx

^a^Primary model: log-binomial regression with generalized estimating equation (GEE) with adjustment of the baseline value of the analyzed outcome and clustering. The logistic regression with GEE will be employed as the alternative method in case of non-convergence, with indirectly derived relative risk reported.

^b^RR: relative risk.

^c^HbA_1c_: glycated hemoglobin.

^d^FBG: fasting blood glucose.

^e^BP: blood pressure.

^f^Only systolic blood pressure at baseline and clustering were adjusted in the primary model for BP control.

^g^LDL-C: low-density lipoprotein cholesterol.

^h^Composite diabetes control: defined as HbA_1c_ level <7.0%, BP <140/80 mmHg and LDL-C <2.6 mmol/L.

^i^No baseline variable was adjusted in the primary model for the composite diabetes control.

**Table 3 table3:** Estimated effects of intervention compared to control on the change from baseline of continuous outcomes.

Secondary continuous outcome		Control, mean (SD)	Intervention, mean (SD)	Primary model^a^	
				Mean differences (95% CI)	*P* value

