**Methods:**

The ROADMAP study adopts a community-based, cluster randomized controlled trial design that compares the effectiveness of a tiered diabetes management model on diabetes control with usual care among patients with diabetes over a 1-year study period. The primary outcome is the control rate of glycated hemoglobin (HbA_1c_) <7% at 1 year. Secondary outcomes include the control rates of ABC (HbA_1c_, blood pressure, and low-density lipoprotein cholesterol [LDL-C], individual and combined) and fasting blood glucose, and the change in each outcome. The primary analysis will be the log-binomial regression with generalized estimating equation (GEE), which accounts for the clustering within communities, for binary outcomes and linear regression with GEE for continuous outcomes. For both, the baseline value of the analyzed outcome will be the covariate. The other covariate further adjusted models and the repetitive models after multiple imputation (when more than 10% of observations in HbA_1c_ after 1 year are missing) will be used for sensitivity analysis. Five prespecified subgroup analyses have also been planned to explore the heterogeneity of the intervention effects by adding the subgroup variable and its interaction with the intervention to the primary model.

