### Outcomes

The primary outcome is the HbA_1c_ control rate (percentage of patients achieving HbA_1c_ <7.0%; target A) at 1 year. The secondary outcomes include the percentage of patients achieving both systolic blood pressure <140 mmHg and diastolic blood pressure <80 mmHg (target B); the percentage of patients achieving LDL-C <2.6 mmol/L (target C); the optimal control rate of the combined ABC targets as previously defined; the percentage of patients achieving FBG <7.0 mmol/L; the changes in levels of HbA_1c_, BP, LDL-C, and FBG; and the subtype-specific and overall hypoglycemia episodes [9]. Other outcomes are health-related quality of life measured by the EuroQol questionnaire EQ-5D-3L (3-level version of EQ-5D) [10,11], the mean change in the scores of the summary of diabetes self-care activities questionnaire [12], the development of any self-reported onset of new comorbidities and diabetic complications during follow-up, concomitant medications, and direct medical cost.

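### The plan states two different primary models for the combined ABC outcome: the text adjusts for baseline values, while Table 2 adjusts for none (and, more narrowly, keeps only systolic pressure for BP control)

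*SAP article*

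**What the plan says.** The SAP article's section Analysis for Binary Categorical Outcomes lists the binary secondary outcomes: control of FBG, of BP and of LDL-C, "and the optimal control rate of combined ABC targets". It gives all of them one model: "A log-binomial regression with GEE and including baseline continuous values of the analyzed outcome variable as covariate (model 1) will be used".

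The Methods part of the abstract states the same rule for binary and continuous outcomes, with no exception: "For both, the baseline value of the analyzed outcome will be the covariate". Footnote a of Table 2 repeats it, describing the primary model as fitted "with adjustment of the baseline value of the analyzed outcome and clustering".

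Two later footnotes to the same table depart from the rule:

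- Footnote i, composite: "No baseline variable was adjusted in the primary model for the composite diabetes control".
- Footnote f, BP control: "Only systolic blood pressure at baseline and clustering were adjusted in the primary model for BP control".

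The Outcomes section defines BP control on two measurements, as the percentage of patients "achieving both systolic blood pressure <140 mmHg and diastolic blood pressure <80 mmHg (target B").

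**The concern.** The composite is named in the text among the outcomes that receive baseline adjustment, and Table 2 then removes that adjustment. An analyst following the section and an analyst following the table shell would fit different primary models and report different estimates, intervals and P values. The article exists to fix the methods before database lock, so this choice should not be left open.

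The version without covariates also gives up precision. The Introduction cites under 10% of service recipients meeting all three targets. That is a background figure, not a planning rate, but it suggests that composite events will be few. Baseline HbA1c, SBP, DBP and LDL-C are already collected and appear in the Table 1 shell.

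Model 1 is also the base for model 2, the subgroup models and any imputed analysis, so the ambiguity carries into those results.

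**Working it through.** **1. Can the passages be reconciled?**

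- *Composite.* The text requires baseline continuous values and footnote i allows none. This is not simply a general rule narrowed by a specific one, because the text itself names the composite. The rule also cannot be applied literally: three targets measured on four continuous variables have no single continuous baseline value. The covariate set therefore has to be written out, and it is not.
- *BP control.* Footnote f keeps one baseline BP value. It can be read as saying which value enters the model, so this is a narrower gap than the composite's.
- *Precedence.* The Results section says the table templates were produced before the methods text. This does not settle which version governs.
- *Model 2.* It adds economic level, locality and only those baseline variables that differ between arms at P<.01. It would pick up marked imbalance but does not reliably restore the omitted baseline values.

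**2. The plan's own figure.** Inputs from Sample Size: 288 control and 576 intervention clusters, 19 patients each, ICC 0.15, 40% versus 45%, two-sided 0.05.

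- Design effect: 1 + (19 − 1) × 0.15 = 3.7.
- Effective control size: 288 × 19 / 3.7 = 1,478.9. The intervention arm has twice this, 2,957.8.
- SE (unpooled): √(0.40 × 0.60 / 1,478.9 + 0.45 × 0.55 / 2,957.8) = 0.01568.
- Power: Φ(0.05 / 0.01568 − 1.96) = 89.0% (88.8% with pooled variance).

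The stated 89% reproduces. It concerns the primary outcome, which this point does not touch. The plan gives no power or precision figure for the composite or for BP control.

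**3. Size of the precision loss.** This was simulated with 864 clusters of 19, allocation 2:1, a latent ICC of 0.15 and 30 replicates per setting. The fit was a log-link Poisson model with cluster-robust SE, standing in for the log-binomial GEE. Assumptions not in the document: baseline-to-1-year correlation of 0.3, 0.5 or 0.7; SBP–DBP correlation of 0.6; control rates of about 7.5 to 8% (composite) and about 45% (BP); complete baseline data.

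Mean SE of the log relative risk (ratios use unrounded SEs):

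| Outcome | Correlation | Footnote model | Fuller model | SE ratio | Variance ratio |
|---|---|---|---|---|---|
| Composite: none vs HbA1c, SBP, DBP, LDL-C | 0.3 | 0.0690 | 0.0672 | 0.975 | 0.950 |
| | 0.5 | 0.0677 | 0.0636 | 0.939 | 0.881 |
| | 0.7 | 0.0683 | 0.0589 | 0.863 | 0.745 |
| BP: SBP vs SBP and DBP | 0.3 | 0.0277 | 0.0273 | 0.989 | 0.977 |
| | 0.5 | 0.0265 | 0.0255 | 0.964 | 0.930 |
| | 0.7 | 0.0243 | 0.0222 | 0.916 | 0.838 |

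The SE falls by about 2.5%, 6% and 14% for the composite and by about 1%, 4% and 8% for BP. Adjusting the composite for its baseline yes/no status alone gives about 1%, 3% and 9%. A separate simulation over the same correlation range gave about 1 to 13% for the composite and 1 to 7% for BP. The summary ranges are therefore roughly 1 to 14% and 1 to 8%.

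These ranges move with the assumptions. Runs with ICC between 0.05 and 0.15 and other correlations reached 20% for the composite and 14% for BP. With 30 replicates, the empirical spread of the estimates is too noisy to confirm the smallest differences, so the comparison rests on the mean robust SEs.

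**4. Is the estimate shifted?** For the composite, the mean log relative risk without and with covariates was 0.344 and 0.347, 0.363 and 0.353, and 0.336 and 0.338 at the three correlations. That shows no systematic shift, as expected under randomization.

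**The case against.** The best defence is that footnote a gives the rule and footnotes f and i give deliberate exceptions for two named outcomes. The text promises only a strategy like that of the primary outcome, and its rule has no literal meaning for a composite. On this view the table supplies the detail. For BP control much of this stands: systolic pressure is a baseline BP value, and adding diastolic is a modest gain in precision. For the composite it does not suffice, because the text names that outcome, no exception is signalled there, and no order of precedence is stated.

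A reader might infer that leaving out baseline values biases the composite result. The documents do not support this. Communities are randomized, so the unadjusted relative risk is valid and its interval already carries chance imbalance. A reader might also treat these as key secondary outcomes. The article calls them secondary, with no multiplicity control and no stated power.

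Nor should the gain be expressed as extra patients. With 20% more patients per community, the effective size per cluster goes from 19 / 3.7 = 5.14 to 22.8 / (1 + 21.8 × 0.15) = 5.34, about 4%. A variance ratio translates only into more communities.

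Two practical objections stand:

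- The ITT population requires only baseline gender, age and HbA1c, and the primary analysis does not impute. Adding LDL-C and BP would drop patients who lack those values unless the plan says otherwise.
- A log-binomial model with four continuous covariates is harder to fit. In a check at assumed correlations of 0.5 or more, fitted probabilities exceeded 1 in most runs. The plan already has Poisson and logistic fallbacks for non-convergence.

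**Conclusion.** The concern holds as an inconsistency in the prespecified model, with a modest cost in precision. For the composite the contradiction is plain: one secondary outcome has two stated primary models. For BP control it is a narrower matter of an unexplained choice of covariate.

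The direction of the precision loss is secure. Its size is not a figure from the document: roughly 1 to 14% of the SE for the composite and 1 to 8% for BP control, at assumed baseline-to-1-year correlations of 0.3 to 0.7 and with complete baselines. Nothing here weakens the primary HbA1c comparison. The correction is worth making because it is cheap and removes a choice between two results for the same outcome.

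**What to change.** State one covariate set, in identical terms, in Analysis for Binary Categorical Outcomes and in Table 2, replacing footnotes f and i:

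- Composite, model 1: baseline HbA1c, SBP, DBP and LDL-C as continuous covariates.
- BP control, model 1: baseline SBP and DBP as continuous covariates.

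Two further sentences belong in the same edit:

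- *Missing baseline values.* Keep patients with missing baseline LDL-C or BP in the model, for example by simple imputation of the baseline covariate, and make clear that the no-imputation rule for the primary analysis does not bar this.
- *Non-convergence.* Expect it more often with the four-covariate model and apply the existing Poisson and logistic GEE fallbacks. The Poisson relative risk keeps the relative-risk estimand.

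The cost is two footnotes, two model statements and these two sentences. No new data are needed, and the sample size and primary analysis do not change.

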**The change from baseline of:**					
	HbA_1c_^b^ level, %	x.xx (x.xx)	x.xx (x.xx)	x.xx (x.xx-x.xx)	.xx
	FBG^c^ level, mmol/L	x.xx (x.xx)	x.xx (x.xx)	x.xx (x.xx-x.xx)	.xx
	Systolic blood pressure, mmHg	x.xx (x.xx)	x.xx (x.xx)	x.xx (x.xx-x.xx)	.xx
	Diastolic blood pressure, mmHg	x.xx (x.xx)	x.xx (x.xx)	x.xx (x.xx-x.xx)	.xx
	LDL-C^d^ level, mmol/L	x.xx (x.xx)	x.xx (x.xx)	x.xx (x.xx-x.xx)	.xx

^a^Primary model: linear regression with generalized estimating equation and with adjustment of baseline value of the analyzed outcome and clustering.

^b^HbA_1c_: glycated hemoglobin.

^c^FBG: fasting blood glucose.

^d^LDL-C: low-density lipoprotein cholesterol.

**Table 4 table4:** Incidence and events rate of hypoglycemia by treatment arms.

Hypoglycemia^a^	Control (n=xxxx)			Intervention (n=xxxx)				*P* value^b^	
	Patients	Events	Events/100 patients		Patients	Events	Events/100 patients		
Symptomatic hypoglycemia	xxxx	xxxx	xx		xxxx	xxxx	xx		.xx
Asymptomatic hypoglycemia	xxxx	xxxx	xx		xxxx	xxxx	xx		.xx
Probable symptomatic hypoglycemia	xxxx	xxxx	xx		xxxx	xxxx	xx		.xx
Relative hypoglycemia	xxxx	xxxx	xx		xxxx	xxxx	xx		.xx
Overall hypoglycemia	xxxx	xxxx	xx		xxxx	xxxx	xx		.xx

^a^Hypoglycemia subtypes followed the American Diabetes Association and The Endocrine Society suggested classifications [9].

^b^*P* values will be reported from Poisson regression with generalized estimating equation and with adjustment of baseline count of each hypoglycemia category.

## Discussion

### Summaries

This article presents the detailed statistical analysis plan for the ROADMAP study, which is a clustered randomized controlled trial conducted in diverse areas of China with the purpose of testing the effectiveness of a mobile health platform named *Graded Roadmap* on diabetes control.

The clustered randomized controlled trial design is useful for assessing community-based interventions like the ROADMAP study yet requires careful attention to conduct valid analyses. As such, clustering of outcomes was accounted for when designing the study and, as previously mentioned, will be accounted for in the analysis of the study outcomes. In the study design, the intraclass correlation coefficient was estimated to be 0.15 based on our previous ORBIT study. ORBIT recruited patients who were initiating basal insulin treatment at secondary and tertiary hospitals. The intraclass correlation coefficient may differ from that observed in the studied populations in ROADMAP.

To find out the effectiveness and feasibility of the platform in different regions, four strata were covered by ROADMAP. They are economically developed urban areas, economically developed rural areas, economically less-developed urban areas, and economically less-developed rural areas. Although the economic development level (developed vs less-developed) and locality (urban vs rural) have been included in the predetermined subgroup analysis, more detailed descriptions might be needed for the factorial subgroups.

